#### Ecological momentary assessments

The self-report questionnaires described above assessing longer-lasting characteristics will be complemented with ecological momentary assessments (EMA) intended to measure real-life short-term states. For one week before the intervention (t0), one week after the first component (t1) and one week after the second component (t2), respectively, participants will be asked to complete a series of short online questionnaires, i.e., as many instances of the series as possible for them, as they receive 6 random prompts per day for 7 days. With each prompt, the assessment is available in a time window of 30 min and set to take 2–3 min to complete. Apart from the scale for momentary affect, the included items were developed based on conceptual considerations. All the items are rated on a 7-point scale from 0– not at all to 6– extremely.

*Momentary affect* will be assessed with an abbreviated version of the Positive And -Negative Affect Scale (PANAS) following previous research, that used similar EMA items [64, 65]. It contains 12 items that measure different affective states, for example, “At the moment I feel relaxed.”.

*Coping*: Five items assess coping based on previous research [66]. They measure different emotion regulation and coping strategies such as reappraisal, avoidance or help seeking, for example: “I tried to seek advice or comfort from others.”

##### Momentary burden

Seven items assess the level of distress in different areas of life (family/friends, thoughts/feelings, work/school, memories, leisure, others, and overall burden) in line with the questionnaire in the epidemiological study [50].

##### Resilience

One item assesses how well participants can cope with their current situation.

##### Social interactions

Nine items explore distress in social relationships, whether the participant has had social contact since the last assessment, and for the last significant social situation, the participant’s emotional state, e.g. “In the last social situation, I felt relaxed”. If someone did not have social contact, the reasons were assessed, e.g. avoidance of social contact or preferring to be alone.

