**Methods:**

The efficacy of the app will be tested through a single-centre, two-arm randomized controlled trial, comparing an active intervention group against a waiting list control group. The active group is divided into two subgroups, in which the two components are delivered in a different order to investigate differential effects in a crossover design. Up to 250 emerging adults aged 18 to 25 years with a history of ACE from a general population cohort study will be recruited. The primary objective is to test the efficacy of the app in improving resilience (primary outcome) and well-being (co-primary outcome) compared to a waiting list control group and to examine the stability of these effects. The secondary objectives include testing the efficacy of the app in improving the secondary outcomes, i.e., self-efficacy in managing emotions, problem solving, fear of evaluation, social avoidance, and self-esteem; examining the differential effects of the two components; and assessing the effect of the app on real-life data on resilience, affective states, distress in social interactions and coping strategies. Furthermore, the study will investigate potential moderators (e.g. ACE severity) and mediators of intervention outcomes (e.g. self-efficacy in managing emotions).

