### Secondary objectives

The secondary goals of this study are.

1) to test the efficacy of the FACE self-help app in improving self-efficacy for managing emotions and problem-solving as facets of self- and emotion regulation, fear of negative evaluation and social avoidance as facets of social skills and social information processing, as well as self-esteem (secondary outcomes).

2) to test the differential effects of the self- and emotion regulation (SER) and the social skills and social information processing (SSIP) components on all outcomes. We hypothesize that SER will specifically improve self-efficacy for managing emotions and problem-solving and thus will have a greater effect on these variables than will SSIP. Similarly, we expect that SSIP will specifically improve fear of negative evaluation and social avoidance and thus will have a greater effect on these variables than will SER.

3) We aim to analyse the effects of the FACE self-help app on real-life ecological momentary assessment data in affective states, distress in several areas of life, social interactions, the use of coping strategies and resilience. We expect that the FACE self-help app will improve these variables compared to the waiting list control group.

4) Finally, we assess the degree of satisfaction of the participants with the FACE self-help app.

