	**Introduction module** (always available) - Explanation of how the app works - Formulation of personal goals - Psychoeducation on prevalence, types, and consequences of ACE - Contact information on where to find additional help	
	**Toolbox with short exercises for daily life** Exercises and suggestions connected to - emotion regulation, i.e. to distraction, relaxation, encouragement, perspective and enjoyable activities (SER component) - social relationships, i.e. to personal boundaries, feeling at ease before, during and after social situations, social challenges and enjoyable activities (SSIP component)	
**Thematic Modules**	**SER Component**	**SSIP Component**
1. Psychoeducation and personal relevance of topics	- Importance of emotions for one’s life, thoughts, and behaviour - Emotion regulation and ACE	- Importance of relationships and reflection on status quo of personal relationships - Relationships and ACE
2. Promoting behavioural skills	- Emphasis on the active influencing of situations, behaviour and feelings to minimise negative and push positive emotions	- Emphasis on the identification and active promotion of social skills
3. Identification and resolving of dysfunctional cognitive patterns	- Identification of biased automatic perception and thought patterns, and how to counter them	- Identification of biased expectations towards social situations and interpretations of other people’s behaviour, and how to counter them
4. Promoting skills and long-term improvement	- Problem solving and the creation of favourable conditions for one’s emotional experience	- Dealing with difficult social situations and the building of positive social experiences - Learning to play to one’s social strengths
	**Final module/Farewell** - Summary and reflection of what has been learnt - Reiteration of contact information to find additional help - Tips on how to continue	

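### EMA ratings of the last social situation appear to exist only after contact, which the app is meant to change, so comparing them between arms can mislead in either direction

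*Protocol article*

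**What the plan says.** The abstract lists as a secondary aim "assessing the effect of the app on real-life data on resilience, affective states, distress in social interactions and coping strategies". Secondary objective 3 covers affective states, distress, social interactions, coping and resilience in the EMA data, and states: "We expect that the FACE self-help app will improve these variables compared to the waiting list control group".

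The EMA section on social interactions describes the items: "Nine items explore distress in social relationships, whether the participant has had social contact since the last assessment", and then "for the last significant social situation, the participant’s emotional state, e.g. “In the last social situation, I felt relaxed". It continues: "If someone did not have social contact, the reasons were assessed, e.g. avoidance of social contact or preferring to be alone". The section on momentary burden separately includes a distress item for family and friends. Neither that item nor the item on distress in social relationships carries a stated contact condition.

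Avoidance is a target of the intervention. Secondary objective 2 says "we expect that SSIP will specifically improve fear of negative evaluation and social avoidance". Table 1 lists among the contents of the SSIP component "Dealing with difficult social situations and the building of positive social experiences", and its toolbox includes social challenges as well as enjoyable activities.

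For analysis, the article names linear mixed models with maximum likelihood (Statistical analyses) and multiple imputation depending on the analysis (Handling of missing data and dropout).

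**The concern.** If the situation ratings are collected only after contact, they describe a set of encounters that is partly chosen after randomisation. The app is meant to change that choice. A participant who stops avoiding people contributes ratings of encounters that a similar control participant would have skipped. Randomisation balances the people in the two arms. It does not balance the encounters that get rated.

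The named missing-data methods do not resolve this. Maximum likelihood and multiple imputation address values that exist but were not observed. A feeling during an encounter that never took place is undefined, and imputing it would create data rather than recover it.

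At stake is how the social-interaction part of objective 3 is read. If newly entered encounters are harder than the usual ones, a working app can show a diluted or adverse difference on these ratings. If they are easier, it can look better than it is.

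**Working it through.** **No stated figure to reproduce.** The article gives no contact rate, EMA mean or EMA standard deviation. Its sample sizes of 24 and 162 do not enter here. What follows is an illustration: the 0 to 6 scale comes from the EMA section and all other inputs are assumed. Ratings are scored so that higher means more distress; an item on feeling relaxed would be reversed.

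**Model A: mixture of contacts.** Let *c* be the share of prompts with contact in either arm, *d* the extra share entered only in the app arm, *g* the difference in distress between added and usual contacts, and *t* the true reduction in distress at every contact. Then

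observed difference (app minus control) = −*t* + *g* × *d* / (*c* + *d*).

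With *c* = 0.60 and *d* = 0.10, the multiplier is 0.10 / 0.70 = 0.143. With no true effect (*t* = 0):

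| *g* | Shift in contact-only mean |
|---|---|
| +1 | +0.14 |
| +1.5 | +0.21 |
| +2 | +0.29 |
| +3 | +0.43 |
| −1 | −0.14 |

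As a direct check of the second row, take a control mean of 2.0 and added contacts at 3.5: (0.60 × 2.0 + 0.10 × 3.5) / 0.70 = 2.21, against 2.00. In that case a true reduction below 0.21 changes sign, and a larger one shrinks by 0.21. Over *c* = 0.50 to 0.70, *d* = 0.05 to 0.20 and *g* = 1 to 3, the shift runs from +0.07 to +0.86.

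**Model B: selection.** Let distress have standard deviation 1.5. Contact occurs when a normally distributed avoidance propensity falls below a threshold, and that propensity has correlation *r* with distress. With contact rate *p* and *a* the standard normal *p*-quantile, mean distress given contact is μ − *r* × 1.5 × φ(*a*) / *p*.

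- *p* = 0.60: 1.5 × φ(*a*) / *p* = 0.966
- *p* = 0.70: 1.5 × φ(*a*) / *p* = 0.745
- Shift when contact rises from 60% to 70%: *r* × (0.966 − 0.745) = 0.221 × *r*

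| True change | Observed, *r* = 1 | Observed, *r* = 0.5 | Observed, *r* = 0 |
|---|---|---|---|
| −0.1 | +0.12 | +0.01 | −0.10 |
| −0.2 | +0.02 | −0.09 | −0.20 |
| −0.3 | −0.08 | −0.19 | −0.30 |
| −0.5 | −0.28 | −0.39 | −0.50 |

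A negative *r* moves the result the other way: at *r* = −0.5, a true change of −0.2 would appear as −0.2 − 0.11 = −0.31.

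Both models agree. The distortion grows with the change in contact and with the difference between added and usual encounters, and it vanishes when either is zero.

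**The case against.** Several points on the other side are fair.

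- **The skip logic is inferred.** The article does not print the branching, and the last significant situation could lie before the previous prompt. If the emotional-state items are asked at every prompt, the problem is smaller. The sentence on reasons for no contact makes the conditional reading the more natural one, but it remains a reading. This stands.
- **Not all EMA social distress is conditional.** A reader might infer that social distress is recorded only after contact and that the whole social part of objective 3 is compromised. The article does not support that: the items on distress in social relationships and on family/friends burden have no stated contact condition. This stands.
- **The direction is open.** A reader might infer that a working app must look harmful. That requires added contacts to be harder than usual ones, and a sign reversal also requires a true effect that is small relative to the shift. Table 1 lists positive and enjoyable social experiences beside the difficult ones, so added contacts could be easier. This stands. The Background does describe effects of digital interventions as often only small to moderate, so masking is not far-fetched.
- **No contact-only comparison is written down.** An analysis plan may already handle this, and the article collects contact and the reasons for its absence. That makes the point easy to settle. It does not remove it, because the article predicts improvement in social interactions and names only methods that leave the selection in place.
- **Reduced avoidance would still be visible.** The questionnaire subscale measures it separately. That limits the damage but does not make the situation ratings comparable.

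A reader might also extend the point to the SER-versus-SSIP contrast at t1. The specific component hypotheses name questionnaire outcomes only, and no EMA component contrast is spelled out. If one is run on the situation ratings, the same caution applies.

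**Conclusion.** The point holds in a limited form. Arm comparisons of the situation ratings probably condition on contact, which the app is expected to change, so they can be biased in either direction. Under the assumed rise from 60% to 70% contact, the shift is 0.14 to 0.43 points on the 0 to 6 scale when added contacts are 1 to 3 points harder. That is enough to hide or reverse a small true benefit but not a large one. These figures show an order of magnitude, not a forecast, because every contact rate and distress value is assumed. The conclusion also rests on the inferred branching.

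The primary outcomes, the questionnaire measure of social avoidance and the social EMA items without a contact condition are unaffected. What changes is what objective 3 may conclude from one subset of items.

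**What to change.** For objective 3, base the main social EMA comparison on measures defined at every answered prompt, and compare them by arm:

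1. the social-distress items without a contact condition (social relationships, family/friends burden);
2. the proportion of prompts with contact;
3. the proportion of prompts with avoidance as the reason for no contact, keeping a preference for being alone as a separate category.

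Present situation ratings given contact only beside these, as descriptive, and do not treat them alone as evidence of benefit or harm. State whether the emotional-state items are shown when no contact is reported.

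A composite of contact and distress may be added as a sensitivity analysis. It needs a cut-point set in advance and loses information by dichotomising the 0 to 6 ratings, so it should not be the main measure.

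The cost is some analysis wording and a little extra analysis of items already collected. No new data are needed.

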#### Usage data and data from the FACE epidemiological study

Participants’ use of the FACE self-help app (logins, number of visits and time spent on modules/submodules pages) will be recorded as a measure of adherence. Furthermore, the data assessed in the FACE intervention study will be linked to the data assessed in the FACE epidemiological study, which included, among other variables, ACE and sociodemographic variables.

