### Participants and procedures

Participants will be recruited between August 2023 and July 2024 from the FACE epidemiological study sample, which is based on a random list-based general population sample of emerging adults aged 18–21 at baseline in German-speaking Switzerland. This part of the study was described in detail in an earlier study protocol [50]. The FACE epidemiological study assesses different types of ACE, i.e., emotional abuse and neglect, physical abuse and neglect, sexual abuse, witnessing domestic violence, household dysfunctions but also peer verbal, physical and sexual abuse.

Emerging adults who reported a history of ACE in the FACE epidemiological study will be invited to participants in the self-help app evaluation study via an e-mail from the study collaborators. The e-mail invitation contains a written study information regarding the procedure and study content as well as a link to schedule an appointment for the interview. In the interview, the suitability of the self-help app for the situation of the respective emerging adult will be discussed and, in case of an acute crisis, participants will be informed about support and health-care services such as psychiatric outpatient clinics. After sending back the signed written informed consent to the study team, participants will receive the online questionnaires.

The inclusion criteria are (1) self-reported ACE; (2) written informed consent; (3) the possession of a smartphone; (4) mastery of the German language; (5) an age between 18 and 25 years. The exclusion criteria are (1) acute suicidality and (2) the inability to follow the procedures of the study, e.g. due to comprehension problems, visual impairment, lack of sufficient motor skills, or severe psychological or somatic disorders that require immediate treatment that impedes continuous work on the self-help program. These points will be discussed with the participants during the screening procedures.

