### Statistical analyses

Analyses will be conducted according to the intention-to-treat paradigm. Additionally, we will conduct per-protocol analyses, including participants who complete baseline and post-intervention assessments and log into at least four modules defined as minimal therapeutic exposure. The significance level will be two-sided at *p* ≤ 0.05. To test the efficacy of the intervention in the intervention group compared to the control group, we will use linear mixed models. The differential effects of the SER and SSIP components will then be tested with interactions between the component and time. These analyses will model random slopes and intercepts for participants, test the fixed effects of the condition, as well as repeated assessments over time, using data from all participants. Linear mixed models have the advantage that they can account for missing values through maximum likelihood estimation [74]. Cohen’s d and f will be calculated as effect sizes. Furthermore, we will calculate Reliable Change Indexes [75].

Potential predictors and moderators of intervention outcome, such as gender or ACE severity will be analysed using multiple linear regressions. To analyse the mediation hypotheses and the longitudinal interplay of the variables, we will conduct path and structural equation analyses. Analyses will be conducted in SPSS, R and Mplus. There are no statistical stopping rules in this trial.

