The primary aim of this study is to assess the efficacy of the app in enhancing resilience and well-being as well as other outcome variables in emerging adults with ACE. Additionally, the results will offer insights into the differential impact of the SER and SSIP components on fostering resilience and well-being and secondary outcomes such as self-efficacy for managing emotions, problem-solving, or fear of negative evaluation. The FACE intervention study is embedded in a three-wave epidemiological study to investigate emotion regulation and social information processing as mechanisms that link ACE with psychosocial functioning in emerging adulthood [50]. The epidemiological study based on a random population sample is used to identify emerging adults with a history of ACE who then are invited to take part in the intervention. Thus, the sample of the intervention study may include participants who would not have sought help on their own and who may be less self-selective than samples in intervention studies with a passive recruitment strategy. Moreover, the longitudinal epidemiological data also offer a broad basis for identifying predictors and moderators of treatment outcomes, such as the type and severity of ACE or previous help-seeking.

In addition to the epidemiological data, the retrospective self-report questionnaires for evaluating the app are complemented with EMA data on affective states, social interactions and coping strategies before and after the intervention as well as between the two components. The EMA data can detect context-dependent associations between emotion regulation, social information processing and psychosocial functioning in daily life. It provides real-life data for the evaluation of the app that is less prone to memory bias and can provide ecologically more valid insights into the effects of the app. Thus, by drawing on the longitudinal epidemiological and the EMA data, the FACE study extends the existing knowledge on self- and emotion regulation and social information processing as mechanisms for fostering resilience in emerging adulthood.

Limitations of the study are that self-help interventions have high dropout rates and that the effect sizes are lower than in blended counselling interventions [79, 80]. Furthermore, all the data from the participants are self-reported and thus subject to different types of bias, notably social desirability bias and non-response bias.

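### The efficacy model is described without ACE severity or gender, although both are linked for all participants; prespecifying them gives a small precision gain and a more plausible missing-data assumption

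*Protocol article*

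**What the plan says.** All statements are in the Methods of the protocol article unless noted.

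- **Source of participants** (Participants and procedures): everyone is recruited "from the FACE epidemiological study sample, which is based on a random list-based general population sample of emerging adults". Self-reported ACE is an inclusion criterion.
- **Linked data** (Usage data and data from the FACE epidemiological study): trial data are joined to the cohort data, "which included, among other variables, ACE and sociodemographic variables".
- **Efficacy model** (Statistical analyses): linear mixed models with random intercepts and slopes that "test the fixed effects of the condition, as well as repeated assessments over time, using data from all participants". No baseline covariate is named.
- **Missing values in that model** (same section): "Linear mixed models have the advantage that they can account for missing values through maximum likelihood estimation".
- **Use of the two variables** (same section): predictors and moderators "such as gender or ACE severity will be analysed using multiple linear regressions".
- **Other missing-data provisions** (Handling of missing data and dropout): missing-data patterns will be explored, multiple imputation used for some analyses, and the effect of imputation examined in sensitivity analyses. The imputation variables are not listed.
- **Expected attrition** (Discussion): "self-help interventions have high dropout rates". No rate is given.

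**The concern.** The article singles out two baseline variables that may predict outcome, and its Background ties ACE to lower resilience, the primary outcome. Both variables should be on file for every randomised person, including those who never return a post-baseline questionnaire. The model that answers the primary question is nevertheless described without them.

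Two things follow. First, outcome variance that these variables explain stays in the error term. Second, likelihood estimation is protected against missing data only conditionally on what the model contains. Here that is arm and the observed outcome values. If ACE severity drives both missingness and later outcome, and does so unequally by arm, missing at random may hold given ACE severity but fail without it.

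**Working it through.** **1. The plan's own figures.** G*Power within-between interaction, with λ = N·f²·m/(1−ρ), m = 3, ρ = 0.6, α = 0.05 and power 0.80:

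- f = 0.25, two groups: N = 23 is the first to reach 80%, rounded to 24 for equal groups. At N = 24, λ = 24 × 0.0625 × 3/0.4 = 11.25 with df 2 and 44.
- f = 0.10, three groups: N = 162, with λ = 162 × 0.01 × 3/0.4 = 12.15 and df 4 and 318.

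Both stated sizes (24 and 162) reproduce. Neither involves a covariate, so this point does not change them.

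**2. Precision.** Let p be the partial correlation of the covariate with the t2 outcome given t0. The standard error is multiplied by √(1−p²), and the equivalent gain in sample size is 1/(1−p²) − 1. The values of p are assumed. Power is for d = 0.3, 83 versus 166 participants (about 250 at 1:2), and residual SD √(1−0.6²) = 0.8 before the covariate.

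| p | SE factor | SE reduction | Equivalent extra N | Power |
|---|---|---|---|---|
| 0 | 1 | – | – | 79.7% |
| 0.1 | 0.995 | 0.5% | 1% | 80.1% |
| 0.2 | 0.980 | 2.0% | 4% | 81.2% |
| 0.3 | 0.954 | 4.6% | 10% | 83.3% |

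At d = 0.5 power is 99.6% before and 99.7-99.8% after. The gain is small because the t0 outcome is already among the repeated assessments.

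**3. Missing t2 data.** The article gives no dropout rate, no link between ACE and dropout, and no correlation between ACE and outcome, so every input here is assumed except r = 0.6. The true effect is 0.50 SD. Unless the row says otherwise, ACE severity correlates −0.30 with the outcome at t0 and t2. The table shows the large-sample likelihood estimate without ACE severity, first with t0 and t1 observed, then with only t0 observed.

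| Scenario (t2 missing: app / waiting list) | t0 and t1 | t0 only |
|---|---|---|
| Same dependence on ACE (OR 2 per SD), 22% / 22% | 0.500 | 0.500 |
| Same dependence, 41% / 22% | 0.508 | 0.512 |
| App arm only, OR 2, 41% / 20% | 0.518 | 0.530 |
| App arm only, OR 2, ACE correlation only −0.10 | 0.509 | 0.512 |
| App arm only, OR 3, 42% / 20% | 0.531 | 0.548 |
| Opposite dependence in the two arms, 41% / 22% | 0.530 | 0.548 |
| App arm only, OR 2, ACE correlation −0.45 at t2 | 0.552 | 0.571 |
| Same dependence, 41% / 22%, effect lower by 0.15 per SD of ACE | 0.536 | 0.550 |

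With ACE severity included, its slope estimated within each arm, all estimates lie between 0.499 and 0.503.

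**Hand check of row 3, t0 only.** The coefficient of ACE on t2 given t0 is (−0.30 + 0.6 × 0.30)/(1 − 0.30²) = −0.12/0.91 = −0.132. With OR 2 per SD and 41% missing, completers in the app arm have mean ACE about −0.693 × 0.22/0.59 = −0.26 SD, where 0.22 is the average of π(1−π) and π is the dropout probability. The part not explained by t0 is −0.26 × 0.91 = −0.24. The bias is −0.132 × −0.24 ≈ +0.03, as in the table. With −0.45 at t2 the coefficient is (−0.45 + 0.18)/0.91 = −0.297, and the bias is 0.297 × 0.24 ≈ +0.07.

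**Direction.** If lower instead of higher ACE severity went with loss in the app arm, row 3 would by symmetry give −0.03.

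**Against the standard error.** With 20% and 41% missing, about 66 and 98 participants have t2 data, so SE ≈ 0.8 × √(1/66 + 1/98) = 0.127. A bias of 0.03 is about a quarter of that; 0.07 is a little over half.

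**Limit of simple adjustment.** With one ACE slope common to both arms, the bias vanishes in every row except the last. There about +0.03 of the +0.05 (t0 only) remains, because the effect itself varies with ACE severity.

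**The case against.** The strongest reply is that this is a condensed article and covariate lists usually belong in the analysis plan. The text says which effects will be tested; it does not say that covariates are excluded from the model or from imputation. This has force: nothing stated is wrong, and a full plan may already name the variables. What remains is that the article does assign gender and ACE severity a place, and that place is a separate regression.

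A reader might go further and infer that the primary estimate is biased, and in favour of the app. The documents do not support that.

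- Randomisation makes the unadjusted comparison valid. Bias needs missing t2 questionnaires related to ACE severity differently by arm (or at different rates, or with effect modification), and ACE severity predicting t2 beyond the observed outcomes.
- Leaving the app is not the same as a missing outcome. Dropout is defined as active withdrawal, everyone else is still invited to the later questionnaires, and reminders are sent.
- The remark on high dropout is general. It gives no rate, no difference between arms and no link to ACE.
- The variables are called potential predictors, and moderation by ACE is exploratory with no direction stated. The sign could go either way.
- Multiple imputation and sensitivity analyses are already planned and could use the linked data.

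All participants report ACE, which may also narrow its range and weaken it as a predictor. The article says less about gender as a predictor than about ACE.

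**Conclusion.** The point holds as a low-cost improvement to the stated model. ACE severity and gender are available in principle for all randomised participants and are named as potential predictors, but the described efficacy model does not use them. Adjustment is worth about 0.5-5% in standard error if the partial correlation given baseline is 0.1-0.3.

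The missing-data benefit is conditional. The possible bias is 0 when dependence and rates are equal in both arms, about 0.01-0.03 SD in the milder scenarios, up to 0.05 SD with stronger dependence or effect modification, and about 0.07 SD in the strongest case examined. All these figures rest on assumed dropout rates, odds ratios and ACE-outcome correlations, and the direction is not established. The stated sample sizes are unaffected.

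**What to change.** Before outcome data are seen:

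1. In the primary linear mixed model, add ACE severity (one named index, mean-centred, from a cohort wave completed before randomisation) and gender, each with its interaction with time.
2. Include the same variables in any multiple-imputation model.
3. Report the model without them as a sensitivity analysis.
4. Keep the ACE-by-condition-by-time term for a sensitivity or moderator analysis. It covers effect modification, which simple adjustment does not fully handle, but placing it in the primary model is debatable.

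The cost is a sentence or two in the plan and a few degrees of freedom. With time as three categories (t0, t1, t2) and gender in two, that is 3 parameters per covariate, 6 in all. No new data are needed, because the linkage is already planned.
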